#### Training phase

Details are provided in Table 4. Briefly, training consists of on-site accredited and non-accredited training (120 h in total) delivered by registered health professionals with Certificate IV qualifications in training and assessment, advanced skills in ear and hearing health screening checks and knowledge of the 2020 Otitis Media Guidelines for Aboriginal and Torres Strait Islander children [17] and the CARPA manual [26].

#### Integration phase

Ear Health Facilitators who are selected for employment will transition to a health service integration phase, supported by the HfLI training team (Table 4).

#### Employment phase

Service delivery (Table 4). Briefly, the Ear Health Facilitator(s) will obtain informed consent for ear and hearing surveillance of at least 100 children every 6 months. Otoscopy, tympanometry and hearScreen findings will be entered into the child’s electronic health record (PCIS or Communicare). A diagnosis and care plan will be made in consultation with the child’s doctor, nurse or Aboriginal health practitioner. The Ear Health Facilitator will assist with implementation of the care plan with the family. The Ear Health Facilitator will support families and children to improve school attendance and support teachers who have children in their class who need ear or hearing assistance.

Ear Health Facilitators who resign or lose their job will not be replaced. If there is more than one Ear Health Facilitator employed in the community (i.e. job sharing), the remaining employee will be offered a higher full time equivalent. Alternatively, the health service may employ an Ear Health Trainee who successfully completed the Cert II and clinical competency training; however, the service must deliver the integration phase according to the HfLI protocols. The health service will be reimbursed by the HfLI for employment of the Ear Health Facilitator(s) until the end of the project.

Regular 6-monthly 1-day refresher training workshops for Ear Health Facilitators will be a part of the HfLI program during the employment phase. Sustainability will be measured.

We do not anticipate discontinuing or modifying the HfLI. An independent Data Safety and Monitoring Board (iDSMB) will review progress of the trial. The terms of reference will include stopping rules regarding safety concerns. The HfLI will cease in a community if the Community Reference Group, the Local Authority and the community health and education services request this in writing (i.e. participant withdrawal). Communities will not be replaced.

Sustainability of the workforce is a key goal and retention of Ear Health Trainees and Ear Health Facilitators critical to the HfL Initiative concept. Strategies to improve adherence include casual payment for Ear Health Trainees and payment of Ear Health Facilitators salaries. Adherence to HfLI protocols (attendance, integration phase, refresher training, health and education services) will be evaluated by the training team (via time sheets), HfLI champions (via interviews) and the regular review of aggregated administrative data (ear and hearing screening and diagnosis, follow-up and school attendance).

There will be no restrictions on concomitant activities in participating communities including concomitant employment and training, clinical services such as audiology, speech therapy, surgeries and all other relevant care and education assistance.

### Outcomes

#### Primary outcome—surveillance enhancement

For the resident population of 0- to 16-year-old children, we will report the proportion who have at least one ear *observation,* and the proportion who have at least one ear *diagnosis* documented in their medical records within each 6-month period.

### Outcome definitions

#### Resident population

The resident population has a (primary) medical record with the participating community health service.

#### Ear observation

An ear observation is defined as data recorded using otoscopy or video otoscopy with tympanometry or pneumatic video otoscopy. Ear observation data therefore includes visual observations of the tympanic membrane (e.g. colour, position, perforation size, and mobility if using pneumatic otoscopy) and tests of mobility (tympanogram data such as peak height).

#### Hearing observation

A hearing observation is defined as data recorded using parent reported information (scored using structured questionnaires; Parent-Evaluated Listening and Understanding Measure, PLUM or Hear & Talk Scale, HATS) and hearScreen data (pass, fail) [Hearing Australia].

#### Presumptive diagnosis

Presumptive diagnosis is a diagnosis derived from analysis the ear or hearing observation data.

#### Clinical diagnosis

Clinical diagnosis is a diagnosis derived by a health professional from the ear and hearing observation data or by direct clinical assessment.

#### Management plan

A management plan is defined as the actions recommended as a result of a clinical diagnosis or hearing loss assessment.

Ear Health Facilitators will conduct ear and hearing observations. These observations can be made at venues outside the clinic and where appropriate for the family and Ear Health Facilitator. The data will be recorded on standardised forms on tablets or paper, and then entered into the child’s medical record. The Ear Health Facilitator will document whether the child’s ear and hearing observations are normal (no further action) or not normal (refer to the clinic doctor, nurse or AHP for a diagnosis). The health professional will be responsible making the diagnosis and management plan and entering these into the child’s medical record. Appointments for follow-up and specialist referrals will be assisted by the Ear Health Facilitator if required.

#### Secondary outcomes—ear and hearing observations and presumptive diagnoses (in the last 6 months)

For the resident population of 0- to 16-year-old children, we will report the proportion who have had the following: an ear observation attempted; otoscopy, tympanometry or both; a presumptive diagnosis; a clinical diagnosis; and a documented management plan.

For the resident population of 0- to 5-year-old children, we will report the proportion completing parental questionnaires. For the resident population of 5- to 16-year-old children, we will report the proportion with the following: hearScreen tests completed, presumptive hearing loss documented, an appropriate documented management plan and an appropriate documented referral for each specialist service.

#### Secondary outcomes—training progress

For those community members that completed an expression of interest, we will report the proportion who are eligible, enrolled, pass Certificate II in Aboriginal Primary Health Care, meet clinical competency criteria (by child age group), complete integration, are employed as Ear Health Facilitator(s) and the total FTE employed per 200 children.

#### Secondary outcomes—Ear Health Trainee assessment of training course and trainer performance

Qualitative measures: Ear Health Trainees will be asked to provide weekly feedback on each component of the training course (weeks 1 and 2: Cert II modules, weeks 3 to 6: ear and hearing observation training) for each of the following domains: what they enjoyed, most useful things learned for their future role as an Ear Health Facilitator, things that were difficult to understand or learn, valuable knowledge and skills learned, how the HfLI training program can be improved and other comments.

#### Secondary outcomes—trainer assessment of Ear Health Trainee technical skills

The trainers will assess evidence that the Ear Health Trainee can follow procedures and protocols to conduct otoscopy, tympanometry, and hearScreen can communicate effectively with children and caregivers using a client-centred approach, can maintain confidentiality, can maintain infection control principles and can assist in undertaking a health promotion activity in their community.

#### Secondary outcomes—Ear Health Trainee self-assessment

The Ear Health Trainees will make self-assessment scores (5-step ranking) pre-training and post-training in measures of confidence (five questions), knowledge (five questions) and clinical skills (6 questions). We will report the change in self-assessment scores.

### Secondary outcomes—integration and employment

Integration measures will be Ear Health Facilitator workplace attendance, punctuality, data collection and data entry skills (Redcap, PCIS or Communicare), attendance at supervisor meetings, case load and attendance during outreach service visits (audiologist and surgical outreach).

Subgroup analyses will be by child age group (0 to 3, 4 to 5, over 5 years of age) and by the five Priority groups recommended by the 2020 OM Guidelines.

Sensitivity analyses will compare data from control and HfLI intervention periods with or without the integration period.

Participant timeline (Table 2 and Fig. 1)
Control periods: For all communities, the control period begins in year one at unblinding of the first allocated cross-over date (January 2020). For each community, the control period ends at commencement of their training and includes the lead-in phase.Lead-in phase: For each community, the period between unblinding of their allocated cross-over date to commencement of training (3 to 6 months)Transition period: The period between commencement and completion of training (3 months).Integration phase: The period between completion of training and end of integration into the health service (3 months).Intervention period: The period between completion of training (or end of Integration phase in sensitivity analysis) and end of TimePeriod 7.

#### Sample size

Sample size for the SW-CRT is 18 communities, each having at least 100 children 0 to 16 years of age. The sample size calculation is based on the proportion of participants who receive an ear assessment during the study period. The method of sample size calculation for a cohort SW-CRT design [27] was adapted using numerical simulation. Current evidence suggests that about 33% of children under 5 years of age received a completed ear assessment between 2011 and 2016 in the Northern Territory [11]. We would assume an absolute increase of 10% in the proportion of children who receive an ear assessment to be feasible and clinically important. Given a control proportion of 0.329 and an absolute difference of 0.1 using a two-sided test at 5% level of significance, our sample size of average 90 children per cluster (community) per 6 month period will achieve a total sample size of 1620 at 98% power assuming an intra-cluster correlation coefficient (ICC) of 0.06, a cluster auto-correlation coefficient (CAC) of 0.7 and individual autocorrelation (IAC) due to repeated measurement of children receiving ear diagnoses. We conducted sensitivity analysis using different effect sizes, power, ICC and CAC scenarios to determine if our required number of clusters will be adequate for our study. The result indicates that across a range of ICCs (0.02–1), CAC (0.6–0.8), baseline proportions (0.23–0.53) and effect sizes (0.10–0.20) our sample size of 18 clusters (communities) and 5 step lengths will achieve over 80% power to detect absolute increases between 10% and 20%. In the unlikely event of communities withdrawing, our sensitivity analysis shows that we will still have adequate power assuming we end up with 16 communities, allowing for withdrawal of two communities [28].

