8	When and how much: describe the number of times the intervention was delivered and over what period of time, including the number of sessions, their schedule, and their duration, intensity or dose	Training intervention: 120 h delivered on-country during 6 weeks over a 3-month period commencing at date allocated. EHF integration into Health Service: over 3 months during 3 visits by trainer in addition to phone support. Service delivery: Ear and Hearing services intervention: the EHFs (on average 0.5 FTE per community) will screen at least 100 children every 6 months in each community. The EHFs will also assist families and teachers with strategies to enhance school attendance and learning.	Control period half-day workshops will be evaluated via questionnaires.
9	Tailoring: if the intervention was planned to be personalised, titrated or adapted, then describe what, why, when and how	Training: up to five Ear Health Trainees will be paid on a casual basis to undertake the training course. Trainees must not miss more than 2 days of the 24-day course to qualify for employment as an EHF. The trainers who fly-in fly-out are not able to make up for missed training sessions for individuals. The group can negotiate most suitable dates for training to occur, within constraints of the program, flights, accommodation and commitments to other communities. Employment: the fulltime equivalent (FTE) for employment of Ear Health Facilitators will be 0.5 per community (10 FTEs in total). For statistical analyses, the target sample size for each community is 100 children seen per 6 months. Service delivery: priority children will be determined by the service and according to 2020 OM Guideline recommendations.	N/A
10	Modifications: if the intervention was modified during the course of the study, describe the changes (what, why, when, how)	Not at this stage	N/A

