#### Enrolment of child participants

For our primary outcome, the denominator is the number of resident children 0 to 16 years of age. Ethical approval for waiver of individual consent will be sought to retrieve relevant deidentified ear and hearing data from the medical records. A data access agreement will be executed with the relevant health services (Department of Health or ACCHOs) for this purpose.

For child participants receiving the HfLI (ear and hearing health checks by the Ear Health Facilitators), consent will be required. All age-eligible children whose parents consent to participation will be eligible for enrolment. Written informed consent will be obtained by the Ear Health Facilitators who will be trained by the Clinical Research Training Officers. To minimise selection bias, participant consent will be encouraged by multiple parties including Community Reference Group members, the school and health service staff and the Ear Health Facilitators. The open cohort design allows for continuous recruitment of children.

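### The claim of over 80% power up to an ICC of 1 is false as printed, and the 98% base-case power cannot be placed until the 0/1 sequences are reconciled with Table 2 and the training period

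*Protocol article*

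**What the plan says.** The Sample size section gives these planning inputs: "Given a control proportion of 0.329 and an absolute difference of 0.1", "using a two-sided test at 5% level of significance", and "our sample size of average 90 children per cluster (community) per 6 month period". It states that this "will achieve a total sample size of 1620 at 98% power assuming an intra-cluster correlation coefficient (ICC) of 0.06", with a CAC of 0.7 and an individual autocorrelation (IAC) that is named but given no value. It then reports that power exceeds 80% for increases of 10 to 20 points "across a range of ICCs (0.02–1), CAC (0.6–0.8), baseline proportions (0.23–0.53) and effect sizes (0.10–0.20"), and that it remains adequate if two communities withdraw.

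Three other places bear on the design matrix behind those figures:

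- **Table 1 and Allocation sequence generation** print five sequences over seven periods, 0111111 to 0000011, with every period coded 0 or 1. Clusters are split 2:4:4:4:4.
- **Participant timeline definitions** (end of the section on integration and employment outcomes) end the control period when training starts and begin the intervention period when training ends. The transition is "The period between commencement and completion of training (3 months").
- **Table 2** puts training in the second half of TP2, TP3, TP4, TP5 and TP6 for the five groups, and starts integration and employment in TP3, TP4, TP5, TP6 and TP7.

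Statistical methods analyses clusters by their time of switching. It separates training as a third category only in the per-protocol analysis.

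**The concern.** Two things look wrong.

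First, an ICC of 1 means that all outcome variation lies between communities and community-periods, so the number of children contributes nothing. Eighteen communities could not be expected to give over 80% power for a 10-point increase in that case.

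Second, the first 1 in each printed sequence is, on the Table 2 dates, a period of lead-in followed by training, before any Ear Health Facilitator is employed. The last sequence has two HfLI periods in the matrix but only one on the dates. The power section does not say how these months were treated.

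At stake are the stated robustness range and, more importantly, whether the primary analysis counts a period with no facilitator service as intervention. That would dilute the estimated effect as well as change a planning figure.

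**Working it through.** **Inputs.** From the Sample size section: p0 = 0.329, d = 0.10, two-sided 5%, m = 90 per community-period (18 × 90 = 1620, as stated), ICC 0.06, CAC 0.7. From Table 1: five sequences, seven periods, clusters 2:4:4:4:4. Assumption: IAC varied over 0 to 0.9, because no value is given.

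**Method.** Generalised least squares on community-period means, with categorical period effects and one HfLI effect:

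- s² = mean of p(1−p) at 0.329 and 0.429 = (0.2208 + 0.2450)/2 = 0.2329
- variance of a cell mean = s²[ICC + (1−ICC)/m] = 0.2329 × (0.06 + 0.94/90) = 0.0164
- covariance between periods in a community = s²[ICC·CAC + (1−ICC)·IAC/m] = 0.2329 × 0.042 = 0.0098 at IAC 0
- power = Φ(d/SE − 1.96)

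**Step 1: the stated 98%.** On the printed matrix with every cell counted, SE = 0.0267 at IAC 0, so power = Φ(0.1/0.0267 − 1.96) = 96.3%. At IAC 0.5, SE = 0.0243 and power is 98.5%. At IAC 0.9 power is 99.5%. The stated figure is reproduced.

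**Step 2: the ICC range.** As the ICC approaches 1, (1−ICC)/m vanishes and m no longer matters. On the printed matrix, over CAC 0.6–0.8 and baselines 0.23–0.53:

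| ICC | 10-point increase | 20-point increase |
|---|---|---|
| 1 | 16–33% | 50–83% |

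For 10 points from 0.329 at IAC 0, power falls below 80% once the ICC exceeds about 0.10 (CAC 0.6), 0.14 (CAC 0.7) or 0.20 (CAC 0.8).

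If the upper limit was meant to be 0.1, power for 10 points at IAC 0 runs from about 79% to 97%. The low corner is CAC 0.6 with a baseline of 0.43 (78.6%) or 0.53 (79.6%). At IAC 0.5 the range is 82–99%.

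**Step 3: the lead-in/training cell.** At ICC 0.06 and CAC 0.7, for IAC 0 to 0.9:

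| Treatment of the cell | Power |
|---|---|
| Counted as HfLI with full effect (printed matrix) | 96.3–99.5% |
| Counted as control, HfLI from the Table 2 employment dates | 96.3–99.5% |
| Only the 3 training months removed (approximated as half the cell's data) | about 95–99% |
| Whole 6-month cell excluded (0x11111 … 00000x1) | 81.4–93.1% |
| Coded HfLI, half the effect present | 64–79% |
| Coded HfLI, no effect present | 14–17% |

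In the last row the expected estimate falls from 10 points to about 2.3 (IAC 0).

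**Step 4: the assurances if the whole cell is excluded** (IAC 0 to 0.8). At ICC 0.1, 10 points, CAC 0.6–0.8 and baselines 0.23–0.53, power is 56–93%. With 16 communities at ICC 0.06 and CAC 0.7 it is about 68–90%, depending on which two leave; the low end is loss of both communities in the first sequence. On the printed matrix, 16 communities give about 92–99%.

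**Limits.** This is a linear approximation with equal community sizes and a fixed cohort. The half-cell figure is rough, because the outcome is defined over 6 months.

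**The case against.** The strongest reply is that the ICC limit is very probably a dropped decimal. With 0.1 the sentence nearly holds, so the correction is one character. That largely stands, but the printed claim is still wrong, and at 0.1 there is no slack.

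A reader might infer more in four respects, and the documents do not support it:

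- **That the 98% proves training was ignored.** It does not. About 98% also results when only the training months are removed, or when the cell is kept as control on the Table 2 dates.
- **That 81–93% is the correct power.** That range needs the whole cell to be excluded, and no section says so. Half of the cell is lead-in, which the definitions call control, and the main analysis is by time of switching. A 3-month remnant does fit a 6-month outcome poorly, so exclusion is plausible but remains a choice still to be made.
- **That the withdrawal assurance fails.** On the printed matrix it holds comfortably; it weakens only under exclusion.
- **That 90 children per community inflates power.** Table 4 says "For statistical analyses, the target sample size for each community is 100 children seen per 6 months", while for the primary outcome "the denominator is the number of resident children 0 to 16 years of age". The figures differ, but resident counts would raise power. With Table 3 counts scaled to ages 0–16, the two towns assumed at 300 under 14, and the cell excluded, power is about 92% at IAC 0.5, against 88% with 90 children.

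Simulation settings may also sit in a full protocol or analysis plan that is not shown. That excuses a missing detail, but not the conflict between the sequences, Table 2 and the definitions.

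**Conclusion.** The concern holds in two parts.

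The robustness claim is false as printed: at an ICC of 1 the design has 16–33% power for 10 points and 50–83% for 20. This does not depend on the IAC or on the training period. Read as 0.1, the claim is borderline at about 79% in its worst corner.

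The 98% is arithmetically sound for the printed matrix, but that matrix disagrees with the Table 2 dates and with the definition that leaves training in neither condition. Depending on how the lead-in/training cell is handled, base-case power is essentially unchanged (95–99.5%), reduced to 81–93%, or very low (14–17%) if a cell with no effect is analysed as HfLI. Base-case power stays above 80% under full exclusion. The serious risk is therefore leaving the printed coding in the primary analysis, not excluding the cell. These figures rest on the linear approximation and on an assumed IAC of 0 to 0.9.

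**What to change.** 1. Correct the upper ICC limit to the value actually examined, and report the minimum power over the stated ranges.
2. Reconcile the printed sequences with Table 2 and the timeline definitions, and fix how the lead-in/training cell enters the primary analysis.
3. Restate base-case, minimum and 16-community power on that matrix, giving the IAC used. If the whole cell is excluded, expect about 81–93%, 56–93% (ICC 0.1, 10 points) and 68–90% respectively.

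The cost is one re-run of the existing calculation and possibly a less favourable stated figure. No communities are added.

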#### Recruitment

Strategies for recruiting 20 communities (includes two pilot communities) before commencement of the trial involved written applications (where required) and face-to-face consultations with the Aboriginal Medical Services Alliance of the Northern Territory (AMSANT), Aboriginal Community Controlled Health Organisations: Miwatj Aboriginal Corporation, Katherine West Health Board, Sunrise Health, Anyinginyi (Tennant Creek), Ampilatwatja Health Aboriginal Corporation, Central Australian Aboriginal Congress, Wurli Wurlinjang Health Service Board, Local Authorities for each community, Regional Councils (Barkly, Central Desert, East Arnhem, West Arnhem, Victoria Daly, West Daly, Katherine, Central Desert, Tiwi Islands, West Macdonnell) and Land Councils (Central Land Council, Northern Land Council, Tiwi Land Council), senior public servants in the health and education departments of the NT Government, the NT Top End and Central Australian health services, health service managers, primary healthcare managers, Remote Medical Practitioners, the NT Hearing Health Service Outreach Program audiologists and ENT surgical outreach team. NT Department of Education (including Families as First Teachers), Catholic Education NT, and school principals, teachers and/or inclusion support officers in the above communities have also been consulted. A community eligibility form was designed to collect data on feasibility of delivering the HfLI. Information was also obtained from websites. The NT Government’s Bushtel website was used to estimate the population of children 0 to 16 years, confirmed by the health services (Table 3).

